### Sampling method and subject recruitment

Randomization of the participants will conduct based on the district they belong to. The six districts chosen earlier were randomly assigned into the intervention and control groups with 1:1 allocation. Thus, three districts belong to the intervention group, and three are used in the control group. Figure 2 shows the procedures involved in the recruitment of subjects in this study.

**Fig. 2 Fig2:**
[figure not shown]
CONSORT extension for Cluster Trials

In each area, the participant’s name list is a number code by the researcher. Only the researcher has access to the names and codes and is solely responsible for all the records’ safekeeping and confidentiality. Concealment of allocation or a “third-party” assignment will use. The list of these codes without the individual’s names will be sent to a research assistant (RA) to produce a computer-generated randomization list of the participants. The randomization software used is from the web page of Research Randomizer [12].

Participants will recruit based on the districts they represent to prevent communication between the intervention and the control groups and minimize the contamination. For example, if District A has been chosen in the intervention group, the communities in District A will include in the intervention group. As for District B, the communities in district B will consist of the control group. A simple random sampling will identify the respondents based on the household list in six selected districts during the recruitment process. Those who are eligible will be invited to participate in the study.

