### Study design and study location

This study is a two-armed, parallel, single-blinded, cluster-randomized trial. The cluster in this study is defined as a district in Selangor. There are two groups which are the intervention group and the control group. Both groups follow a similar design until the end of the study. The clusters and participants are blinded for the study. The intervention group will receive HEBI, while the control group will receive a non-communicable health program.

Selangor is one of 13 states in Malaysia, located on the west coast of the Malaysian Peninsular. Selangor covers 7930 km2 [8], with a total population of 6.47 million reports to the Department of Information Malaysia, ranking it the most populous state in Malaysia (19.9%). It has a population growth rate, 1.4% and a high level of urbanization (91.4%) [8]. In addition, it has the largest economy in Malaysia in terms of gross domestic product (GDP) contribution, contributing 22.4% of the total Malaysian GDP [8]. The ethnic composition consists of Malay, 52.9%, Chinese, 27.8%, Indian, 13.3%, and other ethnic groups.

The study will carry out in six districts in Selangor state. First, those districts are chosen based on similar backgrounds related to the flood disaster. Then, those districts are ranked based on floods every year and the severity of the disaster using the Department of Irrigation and Drainage Malaysia data. Based on the rank, district Hulu Langat, Hulu Selangor, Kuala Selangor, Sepang, Sabak Bernam and Gombak were included in this study. Then those districts are divided into intervention groups and control groups using a coin toss. As for respondents, they were selected from each household in those districts based on eligibility.

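### Residents join and give baseline data after their district's arm is fixed, and the stated concealment cannot hide that arm, so participation may differ between arms

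*Protocol article*

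**What the plan says.** **Unit and order of allocation.** Under Study design and study location, "The cluster in this study is defined as a district in Selangor". Six districts are chosen and ranked by flood history, and "Then those districts are divided into intervention groups and control groups using a coin toss". Sampling method and subject recruitment confirms it: "The six districts chosen earlier were randomly assigned into the intervention and control groups with 1:1 allocation".

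**Recruitment of residents.** The text after Figure 2 ties recruitment to the district's arm: "if District A has been chosen in the intervention group, the communities in District A will include in the intervention group". It continues: "A simple random sampling will identify the respondents based on the household list in six selected districts during the recruitment process", and then "Those who are eligible will be invited to participate in the study". Under Data collection method, consent forms come next, then T0, then the programme.

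**Concealment and blinding.** The text after Figure 2 says "Concealment of allocation or a “third-party” assignment will use". The mechanism it describes is a list of name codes sent to a research assistant "to produce a computer-generated randomization list of the participants". Study design and study location claims blinding for clusters and participants and mentions nobody else.

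**Roles.** Data collection method assigns both delivery of the programme and data collection at the site to liaison officers. The article does not say who draws the household sample, who invites, or who takes consent.

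**The concern.** In a cluster trial, randomising the districts protects the comparison of districts. It protects the comparison of enrolled residents only if enrolment does not depend on the arm. When people are enrolled after the arm is settled, knowledge of the arm can affect who agrees and how the baseline is answered.

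The two programmes differ in topic: flood preparedness in one arm, non-communicable disease in the other. If the topic, or the recruiter's effort, shows at invitation, people already interested in floods may accept more often in HEBI districts. Knowledge, skills and preparedness are questionnaire scores, so such people would tend to score higher whatever they are taught. The bias would favour HEBI and would not shrink with a larger sample. Adjustment for T0 can reduce a measured imbalance, but it cannot correct unmeasured motivation, or a T0 that was itself answered differently because the arm was known.

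**Working it through.** **1. Order of events.**

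| Step | Where stated |
|---|---|
| Districts chosen and ranked | Study design and study location |
| Districts split by coin toss, three per arm | Study design and study location; Sampling method and subject recruitment |
| Residents sampled from household lists, by the arm their district holds | Text after Figure 2 |
| Eligible residents invited | Text after Figure 2 |
| Consent, then T0 | Data collection method |
| Programme, T1, T2 | Data collection method |

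This rests on the sequence of the account and on the District A example. It does not rest on verb tense, which is mixed throughout the article. Figure 2, which is said to show the recruitment procedures, is not available here and might add detail.

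**2. What each safeguard covers.**

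- *Coded list:* hides names from the research assistant. The arm follows from the district, so it hides nothing from anyone who knows the district. A participant-level randomisation list also has no clear function when districts are the randomised unit.
- *Stated blinding:* covers clusters and participants, not recruiters or liaison officers.
- *Random household sampling:* protects who is approached, not who accepts.
- *Liaison officers:* they must know the arm to deliver it, and T0 is part of the data collection assigned to them.

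**3. Size.** The plan gives no figure for participation. Its sample size does reproduce: 24 per arm, 48 in total; 48 × [1 + 30 × 0.005] = 55.2; 55.2 / 0.66 = 83.6, rounded up to 84. This does not bear on the point. The useful figure is the planned difference: 0.79 − 0.40 = 0.39, or 39 points.

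*Illustration A (all rates assumed).* Half of residents are flood-minded. Of these 60% are prepared, against 20% of the rest, so the population mix is 0.5 × 0.60 + 0.5 × 0.20 = 0.40, matching the plan's control figure. Acceptance in control districts is the same for both types, and HEBI has no effect. With acceptance a (flood-minded) and b (others) in HEBI districts:

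share flood-minded = a / (a + b); prepared at entry = share × 0.60 + (1 − share) × 0.20

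- a = 0.80, b = 0.60: share 0.571; prepared 0.429; gap 2.9 points.
- a = 0.80, b = 0.50: share 0.615; prepared 0.446; gap 4.6 points.

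That is 2.9/39 = 7% to 4.6/39 = 12% of the planned difference.

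*Illustration B (all rates assumed).* Acceptance in HEBI districts depends directly on being prepared, with 40% prepared in every district:

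prepared at entry = 0.40a / (0.40a + 0.60b)

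- a = 0.70, b = 0.60: 0.28/0.64 = 43.75%; gap about 3.7 points.
- a = 0.80, b = 0.60: 0.32/0.68 = 47.1%; gap 7.1 points.
- a = 0.80, b = 0.40: 0.32/0.56 = 57.1%; gap 17.1 points.

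The gap depends heavily on the assumptions. All these gaps are at entry, before any adjustment.

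**The case against.** The strongest defence is that the article already contains real protection. Households are sampled at random. Participants are said to be blinded, and the interest-driven mechanism needs invitees to sense which programme they are offered. Controls receive an active health talk and are measured in the same way. The eligibility criteria leave recruiters little discretion. T0 is measured, and the GEE compares change over time with covariate adjustment. All of this stands as mitigation. None of it stops differential acceptance when the inviter knows the arm, or differing T0 answers when the data collector does.

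A reader might infer more than the documents support:

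- *That the liaison officers themselves recruit.* They are given delivery and data collection. Consent appears in the same section, so the inference is understandable, but no sentence says they sample, invite or take consent.
- *That randomisation no longer protects the comparison.* This ignores the mitigation above. A gap of the size in Illustration A weakens a comparison designed for 39 points; it does not void it.
- *That the article admits this problem.* The Validity subsection mentions selection bias in choosing which organisation goes to which arm. That concerns allocation of units, not residents' participation.

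**Conclusion.** The concern holds in a limited form. As written, the plan enrols residents and takes T0 after their district's arm is fixed. Its described concealment cannot hide a district-level arm, and it states no blinding of those who recruit or collect data. Participation and baseline answers may therefore differ by arm, most plausibly in favour of HEBI.

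The size is unknown, because the documents give no acceptance rates. Illustration A gives about 3 to 5 points; the harsher assumptions in Illustration B reach 17 points. Both assume arm-dependent acceptance in HEBI districts, none in control districts, and no true effect. The likely consequence is a biased estimate, not a reversed conclusion. This is more than omitted detail, because the order of steps is a stated design choice and can be changed.

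**What to change.** Amend Sampling method and subject recruitment (including the text after Figure 2) and Data collection method:

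1. Complete sampling, eligibility check, consent and T0 in all six districts before the third party releases the district arms to the liaison officers. If the toss has been made, the third party holds the result until T0 closes. Alternatively, have existing staff who are unaware of the arm handle invitation, consent and T0.
2. State who samples, invites and takes consent.
3. Use one identical, neutral invitation and consent text in both arms, describing one of two community health education programmes.
4. Reconcile the participant-level randomisation list with allocation by district.
5. Report approached, eligible and consented counts by district.

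Trial registration gives first enrolment as 01 June 2020 and status as recruiting. Where enrolment has already occurred, apply the change to the remaining recruitment, report the counts for all districts, and state the limitation.

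**Cost.** For recruitment still to come, this is mainly a re-ordering of planned steps and one shared text. The main downside is that programmes start only after T0 closes in all six districts; using staff unaware of the arm avoids that wait.

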### Data collection method

The delivery of the intervention is design to address the limitations that occurred during the COVID-19 pandemic. The intervention and data collection will be carried out at the study site by liaison officers. The researcher can use the module and communicate with the liaison officers about the intervention’s flow and data collection. Respondents will give their consent through consent forms. Subsequently, respondents will be provided with a questionnaire to fill out, utilizing baseline data for the study (T0). Immediately upon completion of the health intervention, respondents will be provided with a questionnaire to respond to the immediate post-intervention assessment (T1). Knowledge, skills, and preparedness outcomes will be assessed at this stage. Six months after completing the health education intervention, respondents would be reassessed on the same effects as knowledge, skills, and preparedness (T2).

### Intervention

The intervention arm will receive the Health Education Based Intervention module (HEBI) developed based on the Health Belief Model Theory as in Table 1, consisting of:
i.The two-hour educational talk will be conducted to all participants, including the importance and benefit of disaster preparedness, difficulties during the disaster, joint issues, and steps to success.ii.Educational disaster preparedness video in which the benefits of disaster preparedness will be introduced and demonstrated.iii.Booklets describing the importance of disaster preparedness, written, and published by the Ministry of Health Malaysia, were distributed. It contains practical during disaster and management of ordinary during disaster problem problems.iv.Brainstorming sessions with the researcher also provide for the community to overcome any individual problem.v.The community supports a disaster preparedness support group in which people can contact them personally by phone during the intervention program.

**Table 1 Tab1:** Summary of the Intervention Activities

Stage	HEBI Components	Theoretical Model Constructs	What and How It Is Delivered
Knowledge	i. Group education (health talk and group discussion) ii. Surrogate experimental learning (Brochure, flyer, poster, video)	i. Perceived Benefit ii. Perceived Barrier iii. Self-Efficiency iv. Perceived susceptibility	i. General knowledge about disaster preparedness will be assessed, and all material will be disseminated during the intervention. ii. Perceived benefit and perceived benefit were assessed during the discussion about the disaster preparedness barrier and the benefit of preparedness. iii. A baseline questionnaire will assess every individual before intervention is programmed. iv. The intention of the preparedness will be assessed.
Skills	i. Interactive learning with the community (brainstorming)	i. Cues to action	i. Information related to the advantage and disadvantages of preparedness. ii. Information about disaster preparedness was explaining. iii. Information on HEBI intervention how to prepare individuals for disaster.
Preparedness and implementation	i. First Aid demonstration ii. Field experimental learning with the group (field visit to disaster area at the community level, mapping the vulnerability area at the community level, and revising emergency plans at community level)	i. Cues to action	i. Preparation of the disaster kit was assessed before and after the intervention. ii. Available of emergency contact and plan of action after intervention

#### Control

Data will be obtained in the same way for the control group as it was for the intervention group: baseline (T0), immediate post placebo (T1), and 6 months post placebo (T2). In addition, a non-communicable disease health talk will be provided to the placebo group.

### Outcome assessment

The questionnaire has seven socio-demographic, socio-economic, personal characteristics, knowledge, skills, preparedness, and perceived disaster preparedness. Socio-demographic has six items, socio-economic status has five items, personal characteristic has two items, knowledge has nine items, skills have ten items, preparedness has nine items.

Prompted responses to the nine questions on knowledge were considered for calculating knowledge scores. The total score on knowledge was calculated by combining scores from 9 questions. Score 1 was given if the answer was ‘yes’ and no negative marking was given for ‘no.’ The maximum possible score for the knowledge part was 9. Good knowledge refers to respondents who have scored more than 50% of knowledge questions, and low knowledge refers to respondents who have achieved less than 50% of knowledge questions [13, 14]..

For skills score, each respondent was asked 10-item questions related to their skills towards disaster preparedness. The maximum possible score for the attitude section was 10. Negative skills represent those respondents who have scored less than 50% from skills questions, and positive skills indicate respondents who have achieved greater than or equal to 50% from skills questions [13, 14].

Each respondent was asked if they prepared any particular action to help create better disaster preparedness. Scores were given accordingly, and no negative marking was given. The maximum score possible was 9 [13, 14].

Perceived disaster preparedness questionnaire adapted from a previous study done in Turkey [15]. This questionnaire extracted six perceived which are Self-efficacy (10 items), Cues to action (5 items), perceived susceptibility (6 items), perceived barriers (14 items), perceived benefits (6 items), and perceived severity (4 items). Cronbach’s alpha coefficient for the subscales ranged from 0.90 to 0.74. Therefore, the GDPB scale based on the HBM was found to be a valid and reliable tool.

Respondents completed scales assessing “susceptibility”, “severity”, “benefits”, “barriers”, “self-efficacy” and “cues to action”. All items were scored on a five-point Likert scale from 1 (strongly disagree) to 5 (strongly agree). All subscales measured General Disaster Preparedness Belief (GDPB). Negatively worded statements (4,6,8,9,17-30,31,35,37,38,42,44) were used, the scores on the items were reverse-scored so that a higher score represented more positive disaster preparedness belief. Total score for each item for susceptibility (30), severity (20), benefits (30), barriers (70), self-efficacy (40), and cues to action (50). Responses were scored and categorized as high (75th quartile), moderate (75–25th quartiles), and low (25th quartile).

The GDPB score measured respondent’s positive disaster preparedness beliefs. It was computed by summing up the six subscales (Self Efficacy + Cues to action + Perceived susceptibility + Perceived low barrier (items were reverse scaled) + Perceived benefits + Perceived severity). Thus, it measured six dimensions with 45 items.

### Project monitoring and quality control

#### Validity

Threats to internal validity were taken into consideration in this research. The main threats that are controlled for intervention infidelity. The intervention module, HEBI, will be developed in a way that others can replicate it. It comprises four delivery techniques: health talk, group discussion, demonstration session, and group discussion.

Other threats include threats by history. In addition, there are unplan events between interventions, such as the control group participant knowing some intervention group participants when learning the intervention module’s content and knowledge on disaster preparedness.

Maturation means the participants change during the trial, such as having an emotional event during the answer baseline questionnaire, to make the wrong answer. For example, during post-intervention data collection, having a dynamic fit and answer the questionnaire correctly and confidently. However, they result in an erroneous increase in scores from the test. Thus, intervening’s the actual effect. To counter this problem, get consent before answering the pre-test question and not force potential personnel to participate in the study. There may also be selection bias in choosing which organization will be in the intervention or control groups.

In terms of questionnaire validity, four experts in public health and one expert in medical will do the content validation. Content validity ratio will calculate for each item, with each item obtained a minimum value of 0.5.

The questionnaire will translate to Bahasa Melayu, the researcher’s national language, four experts in public health, and one expert in medical. For face validity, first, the participants evaluate the questionnaire measures what it intends to measure in terms of the questionnaire’s comprehensiveness and clarity. Secondly, whether the questionnaire is simple, easily understood, inappropriate, redundant, or missing items and how likely the questionnaire was to address the research objectives. Third, whether the flow, arrangement, and wording of the questionnaire are reliable. For reliability, the questionnaire was pre-test to ensure reliability before the final version is used.

## Ethical consideration

Ethical clearance obtained from Ethics Committee for Research Involving Human Subjects Universiti Putra Malaysia (Jawatankuasa Etika Universiti Untuk Penyelidikan Melibatkan Manusia (JKEUPM) with JKE approval number UPM/TNCPI/RMC/JKEUPM/1.4.18.2 (JKEUPM). Besides that, written informed consent from the respondents has obtained before the study.

## Data analysis

### Data entry and analysis

Respondents’ responses to distributed questions will be used to enter data. The research assistant will document the response into IBM SPSS Version 25 (Statistical Package for Social Sciences). Before the final review, data cleaning will be performed to look for any missing data or outliers. Then, the data will be translated to long-form for analysis using the Generalized Estimating Equation (GEE). Descriptive and inferential statistics will be used to analyze the data. In descriptive statistics, continuous data will be reported in either a mean with standard deviations or a median with an interquartile range. Categorical data will be represented in percentages, while continuous data will be reported in either a mean with standard deviations or a median with an interquartile range. The histogram, skewness over the standard error of skewness, and statistical tests of Kolmogorov-Smirnov and Shapiro-Wilk normality tests will be used to screen for normality. If the normality test conditions are met, parametric tests will be used to continue the analysis; otherwise, non-parametric equivalents will be used. A significant alpha level of 0.05 will be used for inferential analysis, and *P*-values will be stated as two-sided.

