One of the most established and oldest conceptual frameworks of health behavior is The Health Belief Model (HBM). This model is applied to disaster preparedness efforts, mainly focusing on human behavior [6]. Preparedness efforts focus on changing human behaviors to reduce people’s risk and increase their ability to cope with hazard consequences. Health Belief Model was developed by focusing on the attitudes and beliefs of individuals. There are four main pillars in the Health Belief Model that representing the perceived threat and net benefits. In addition, they have perceived susceptibility, perceived severity, perceived usefulness, and perceived barriers. This model was introduced as auditing for people’s readiness to act. Additionally, cues to action would activate that readiness and stimulate overt behavior. On the other hand, the self-efficacy concept of inefficiently performing is a recent addition to the Health Belief Model [7].

This study will provide a platform for increasing knowledge and promoting correct skills and preparedness toward flood disaster preparedness. This study will also contribute to the body of knowledge on the preparation of flood disasters among the community. This study aims to develop, implement, and evaluate health education-based intervention (HEBI) based on knowledge, skills, and preparedness as the primary outcome and changing of disaster perception (Perceived Benefit, Perceived Barrier, Self-Efficiency, Cues to action) as secondary outcome using the Health Believes Theory Model to improve flood disaster preparedness among the community. The conceptual framework as in Fig. 1.

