### Sample size estimation

The sample size (N) for this study was calculated by comparing the populations of two groups when the endpoint is quantitative. Using the formula by Lameshow and Lwanga (1990):
$$ N=\frac{{\left[{\mathrm{Z}}_{1-\sigma /2}\surd 2\mathrm{P}\left(1-\mathrm{P}\right)+{\mathrm{Z}}_{1-\beta}\surd {\mathrm{P}}_1\left(1-\mathrm{P}\right)+{\mathrm{P}}_2\left(1-{\mathrm{P}}_2\right)\right]}^2}{{\left({P}_1-{P}_2\right)}^2} $$

Where,

N = Sample size estimation

Z_1− σ/2_ = Standard error associated with 95% confidence interval 1.96

Z_1− β_ = Standard error associated with 80% power = 0.842

P_1 =_ Population proportion 1

P_2_ = Population proportion 2

P = P_1 +_ P_2_ / 2

Thus, the calculation below is based on study flood preparedness [9]:

The proportion of follow-up for flood preparedness in the intervention group.

P_1_ = 79.6% = 0.79.

Proportion of follow-up for flood preparedness in control group.
$$ {\mathrm{P}}_2=40.2\%=0.40 $$$$ \mathrm{P}={\mathrm{P}}_{1+}{\mathrm{P}}_{2/}2=\left(0.79+0.40\right)/2=0.59 $$$$ N=\frac{{\left[1.96\surd 2(0.59)\left(1-0.59\right)+0.84\surd 0.79\left(1-0.79\right)+0.40\left(1-0.40\right)\right]}^2}{{\left(0.79-0.40\right)}^2} $$$$ N=3.53/0.15 $$$$ N=24 $$

Taking into account comparison 2 groups.
$$ N=48 $$

Taking into account the design effect = 48 x [1 + (m-1) ICC].

Where m = average cluster size, ICC = intracluster correlation coefficient.

m = 31 [10], ICC = 0.005 based on adjusted ICC for individual- and cluster-level characteristics [10].

Thus, 48 × [1 + (31 – 1)0.005] = 55.2

Adjusting 34% attrition rate [11].

55.2 / 0.66 = 84 final sample sizes estimated for both intervention and control group.

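### Three primary outcomes share one two-sided 0.05 with no primary time point or success rule, and the trial is sized on only one of them

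*Protocol article*

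**What the plan says.** The Background section of the protocol article describes HEBI as "based on knowledge, skills, and preparedness as the primary outcome", with disaster perception as secondary. None of the three is ranked above the others.

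The Data collection method section describes T1, immediately after the intervention is completed: "Knowledge, skills, and preparedness outcomes will be assessed at this stage". The same three are reassessed at T2. The Control section gives the control arm the same schedule.

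The Data entry and analysis section states: "A significant alpha level of 0.05 will be used for inferential analysis". P-"values will be stated as two-sided". The section on the generalized estimating equation (GEE) compares results between and within arms over the time points with covariate adjustment, and names no particular contrast.

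The Sample size estimation section uses one quantity only. Its first input is described as "The proportion of follow-up for flood preparedness in the intervention group", set against the matching control proportion.

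**The concern.** When several outcomes are primary and each may be declared significant at the full 0.05, the probability that at least one is significant by chance exceeds 5%, unless success requires all of them. The article states neither rule, so the error rate of the trial's main claim is undefined.

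The title and aim concern flood preparedness. As written, a gain in knowledge alone, at either time, could be reported as success on a primary outcome even if preparedness at T2 did not differ between arms. The sample size, meanwhile, was worked out for a single preparedness test at full alpha, so it supports neither a correction for multiplicity nor a requirement that all three succeed.

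**Working it through.** **1. Reproduce the plan's sample size.** Inputs from the Sample size estimation section: P1 = 0.79, P2 = 0.40, P = 0.59, z = 1.96 and 0.842, cluster size 31, ICC 0.005, attrition 34%.

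- Numerator: [1.96·√(2·0.59·0.41) + 0.842·√(0.79·0.21 + 0.40·0.60)]² = 3.61. The article prints 3.53.
- Per arm: 3.61 / 0.39² = 23.7, rounded up to 24, so the small difference in the numerator does not matter.
- Both arms: 48. Design effect: 1 + 30·0.005 = 1.15, giving 55.2. Attrition: 55.2 / 0.66 = 83.6, so 84.

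The figure of 84 reproduces. It is for one two-sided comparison at 0.05 with 80% power.

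**2. Count the tests.** Three outcomes with one test each give three tests; this is the firmer count. If each outcome is compared separately at T1 and T2, there are six.

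**3. Chance of at least one false result if any one counts as success.** For k independent tests this is 1 − 0.95^k for either direction and 1 − 0.975^k in HEBI's favour only.

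- k = 3: 1 − 0.95³ = 14.3%; 1 − 0.975³ = 7.3%
- k = 6: 1 − 0.95⁶ = 26.5%; 1 − 0.975⁶ = 14.1%

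The article gives no correlations, so a range was assumed. Simulation of equally correlated normal test statistics (500,000 draws), with no effect on any outcome and each test holding its nominal level, gave:

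| Correlation | 3 tests, either direction | 3 tests, for HEBI | 6 tests, either direction | 6 tests, for HEBI |
|---|---|---|---|---|
| 0 (formula) | 14.3% | 7.3% | 26.5% | 14.1% |
| 0.5 | 12.5% | 6.3% | 20.8% | 10.4% |
| 0.7 | 10.8% | 5.4% | 16.4% | 8.2% |
| 0.9 | 8.4% | 4.2% | 10.9% | 5.5% |

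The single-test references are 5% (either direction) and 2.5% (for HEBI).

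**4. If all three must be significant.** The false-success rate cannot exceed 5%, so there is no inflation. Power changes instead. If each outcome had the planned 80% (an assumption, since only preparedness was sized), the chance that all three succeed would be 0.8³ = 51% under independence, rising to 80% only if the three tests always agreed.

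**5. What a simple correction would cost.** Under Bonferroni, by the article's own formula:

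| Tests | Level per test | Power at 24 per arm | Per arm for 80% power | Final total |
|---|---|---|---|---|
| 1 | 0.05 | 80% (81% as computed) | 24 | 84 |
| 3 | 0.0167 | 65% | 32 | 2·32·1.15/0.66 = 111.5, so 112 |
| 6 | 0.0083 | 55% | 37 | 2·37·1.15/0.66 = 128.9, so 129 |

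**The case against.** The strongest reply is that testing order, adjustment and the success rule are commonly left to the full protocol or the analysis plan. The article's analysis sections refer to a first objective and to second and third hypotheses that it never lists, so a fuller document probably exists. That stands as far as it goes: silence on adjustment alone would not be a finding. But the article does more than stay silent. It declares three primaries, applies one 0.05 to all inference and sizes the trial for one test. A later plan could not add a Bonferroni correction without undercutting the stated 84.

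Several stronger readings are tempting and should not be drawn:

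- *Six tests are specified.* They are not. The outcomes are assessed at T1 and T2, but the GEE section fixes no contrasts, and one group-by-time test per outcome fits the text equally well.
- *The chance of a false claim for HEBI is 11–26%.* That range counts errors in either direction across six tests. For HEBI only, it is 5.5–14%.
- *The inflation is certain.* It arises only if any single result counts as success. The Discussion part of the abstract expects all scores to favour HEBI. That is an expectation and not a decision rule, but it is compatible with requiring all of them.
- *Preparedness can hardly change by T1.* The documents do not support this. T1 follows completion of the whole intervention, and the Intervention section and Table 1 describe several components, including field learning and revision of emergency plans, over an unstated period. Table 1 also has the disaster kit assessed before and after the intervention.

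**Conclusion.** The concern holds in a conditional form. Three outcomes are primary, each is assessed twice after baseline, all share a two-sided 0.05, and no primary time point, testing order or any-of/all-of rule is given.

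Under an any-of rule the error rate exceeds its single-test reference at every correlation tried. The three-test figures are the firmer ones; the six-test figures apply only if T1 and T2 are tested separately. Under an all-of rule the error rate is controlled, and the gap moves to power, which was planned for one outcome. Either way the stated design does not match the stated sample size.

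The sizes rest on assumed equal correlations from 0 to 0.9 and on each test holding its nominal level. The absence of a rule, and the mismatch between three primaries and one sized comparison, do not depend on those assumptions.

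**What to change.** State that the confirmatory test is the arm difference in preparedness at T2, adjusted for baseline, at two-sided 0.05. Test knowledge and then skills at T2 in fixed sequence (or the two by Holm) only if preparedness is significant. Report T1 results as supportive. This keeps the full 0.05 for the construct on which the trial was sized.

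Three things must be settled with it:

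- **Endpoint form.** The sample size uses proportions (79.6% against 40.2%), whereas the Outcome assessment section defines a preparedness score from 0 to 9 and, unlike for knowledge and skills, gives no cut-off. Either define the proportion or base the sample size on the score.
- **Timing of T2.** The abstract gives both 3 and 6 months, while the Data collection method and Control sections give 6. These must be reconciled.
- **Timing of the change.** The Trial registration section lists the trial as recruiting, with first enrolment on 01 June 2020. Record the change as a dated amendment before any outcome data are compared by arm.

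The cost is that formal claims for knowledge and skills become conditional on preparedness. Choosing the test order does not itself raise the sample size; basing the calculation on the score instead of a proportion could.
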